### Outcome measures

The primary outcome measure is clinical pregnancy (confirmed by ultrasound scan 5 to 6 weeks after ET demonstrating at least one gestational sac with fetal heart activity).

Secondary outcome measures are live birth (defined as the delivery of one or more living infants, >20 weeks gestation or 400 g or more birth weight), number of oocytes retrieval (OCR) and the total gonadotropin dose used in the ovarian stimulation cycle. Ovarian responses are defined according to three categories: poor response, three or fewer OCR; average response, 4 to15 OCR; hyper-response, more than 15 OCR.

Clinical data will be collected from the IVF center databases and from the patients by following up at 6 and 40 weeks after ET. Data on TEAS or EA safety as well as any adverse events will be collected from the practitioner treatment notes.

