### Statistical analysis

Baseline subject characteristics are described by descriptive analysis, and the balance among groups or subgroups was assessed by analysis of variance or *χ*^2^-test. To assess effects of TEAS and EA, the *χ*^2^-test will be applied to compare frequencies between groups such as the CPR and LBR, and analysis of variance will be performed to compare continuous parameters (gonadotropin dose for example) between the groups (*α* = 0.05). All of the analyses will be based on both an intention-to-treat analysis (ITT, with all randomized patients) and a treated-per-protocol analysis (TPP, with all randomized patients minus withdrawals). Missing patient data for those that dropped out of the study will be analyzed using the last observation carried forward method. Patients with complete data missing for primary outcomes will be considered as a negative ITT pregnancy result and eliminated in the TPP analysis.

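### Last observation carried forward is prescribed for dropouts although no outcome is measured repeatedly, so the handling of women lost after a confirmed pregnancy is undefined for live birth

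*Protocol article*

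**What the plan says.** In the protocol article, the Statistical analysis section gives one general rule for dropouts: "Missing patient data for those that dropped out of the study will be analyzed using the last observation carried forward method". It names no outcome and excludes none. The next sentence gives a specific rule for the primary outcome: "Patients with complete data missing for primary outcomes will be considered as a negative ITT pregnancy result and eliminated in the TPP analysis". The same section sets the analysis population: "All of the analyses will be based on both an intention-to-treat analysis (ITT, with all randomized patients", so women who drop out must be given a value somehow.

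The Outcome measures section defines four outcomes:

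- The primary outcome is a pregnancy "confirmed by ultrasound scan 5 to 6 weeks after ET demonstrating at least one gestational sac with fetal heart activity".
- The first secondary outcome is "live birth (defined as the delivery of one or more living infants, >20 weeks gestation or 400 g or more birth weight".
- Two further secondary outcomes, one a count and one a cumulative amount, are listed together as "number of oocytes retrieval (OCR) and the total gonadotropin dose used in the ovarian stimulation cycle".

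On data sources it says: "Clinical data will be collected from the IVF center databases and from the patients by following up at 6 and 40 weeks after ET".

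**The concern.** LOCF fills a gap in a series of measurements of one variable. This trial has no such series. The 6-week and 40-week contacts record different things, pregnancy and birth, so a value from the first is not an earlier value of the second. For the oocyte count, nothing precedes aspiration.

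This is a rule that the protocol states, not a detail left for later. If it stays, an analyst must invent a meaning for it. For live birth, the obvious inventions give opposite answers for the same woman. Live birth matters here because the abstract names it beside clinical pregnancy in the aim of the trial. A choice of meaning made after outcomes are known could shift that comparison.

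**Working it through.** The protocol gives no figure for the effect of this rule, so there is nothing to reproduce. The check has two steps.

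**Step 1: is there anything to carry?**

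| Outcome | Measurements | Earlier value of the same quantity |
|---|---|---|
| Clinical pregnancy | one scan, 5 to 6 weeks after transfer | none; has its own missing-data rule |
| Live birth | one event, delivery | none |
| Oocytes | one count at aspiration | none |
| Gonadotropin dose | one total per cycle | none; a running sum is not an earlier total |

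**Step 2: how far apart are the readings for live birth?**

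Inputs from the protocol (Sample size section): clinical pregnancy rate p = 0.20 in control and 0.20 + 0.15 = 0.35 in TEAS.

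Assumed inputs, which the protocol does not give: q = probability of live birth given clinical pregnancy, and L = share of clinically pregnant women lost before delivery. Lost women are taken to have the same q as the others.

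Formulas, per randomized woman:

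- True rate = p·q
- Literal LOCF (pregnancy carried forward as birth) = p·[(1 − L)·q + L]
- Missing as no birth = p·(1 − L)·q

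With q = 0.80, and L = 0.10 in TEAS and 0.02 in control:

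| | TEAS | Control | Difference |
|---|---|---|---|
| True | 0.35 × 0.80 = 28.0% | 0.20 × 0.80 = 16.0% | 12.0 points |
| Literal LOCF | 0.35 × (0.72 + 0.10) = 28.7% | 0.20 × (0.784 + 0.02) = 16.1% | 12.6 points |
| Missing as no birth | 0.35 × 0.72 = 25.2% | 0.20 × 0.784 = 15.7% | 9.5 points |

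Within an arm the two readings differ by p·L. The gap between the two differences is therefore 0.35 × 0.10 − 0.20 × 0.02 = 0.031, or 3.1 points, which agrees with the table.

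Other loss patterns at q = 0.80 (true difference 12.0 points):

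- 10% loss in both arms: 12.3 points under literal LOCF, 10.8 with missing as no birth.
- 2% loss in TEAS and 10% in control: 11.7 and 13.0 points.

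The upward bias within an arm under literal LOCF is p·L·(1 − q). With L of 5% to 10% and 1 − q of 10% to 20%, it runs from 0.20 × 0.05 × 0.10 = 0.1 point to 0.35 × 0.10 × 0.20 = 0.7 point per randomized woman.

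**The case against.** The strongest reply is that the damage is limited, and much of that reply stands.

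- **The primary outcome.** A reader might infer that LOCF contaminates clinical pregnancy, or that the two missing-data sentences contradict each other. Neither follows. A specific rule beside a general one takes precedence for the outcome it names.
- **Pregnancy turned into birth.** A reader might take this to be the protocol's rule. It is only the literal consequence of one reading, because the text does not say how the carrying forward is done. Carrying forward the status of not yet delivered is equally open. A firm claim that the live birth rate will be biased upward is therefore not supported.
- **Gonadotropin dose.** A reader might infer that partial doses will pass for totals and make the active arms look as if they need less drug. The outcome is the dose used in the cycle. In a cycle that stops early, the dose given is the dose used, so it is observed and needs no imputation. A distortion could arise only if a woman's records ended while stimulation continued, and the IVF center databases are a named source.
- **Session attendance.** It is tempting to argue that loss will differ by arm because only the active arms attend sessions. Sessions end on the day of transfer, and the live birth problem arises after the pregnancy scan weeks later. Patients are unblinded, so unequal loss remains possible, but the protocol gives no evidence for it.
- **The alternative rule.** Counting missing as no birth is not free of bias. In the example it misses the true difference by 2.5 points, against 0.6 for literal LOCF. Its merit is that it is defined and matches the rule for clinical pregnancy.

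None of this supplies an earlier value for LOCF to carry.

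**Conclusion.** The point holds, limited to the secondary outcomes and chiefly to live birth. The protocol prescribes a method that cannot be applied as such to any of its outcomes, and so leaves women lost after a confirmed pregnancy without a defined result.

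The bias of literal LOCF is itself modest, at about 0.1 to 0.7 point per arm. The ambiguity is the larger problem: in the unequal-loss example, the choice of reading moves the TEAS-control difference by about 3 points against a true 12.0. These sizes rest on assumed loss rates and an assumed probability of birth given pregnancy; only the pregnancy rates come from the protocol. With small and equal losses the effect would be smaller. This should be fixed, but it does not threaten the primary analysis.

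**What to change.** 1. Delete the LOCF sentence.
2. State that clinical pregnancy and live birth will be ascertained for every randomized woman, including those who withdrew from treatment, from the IVF center databases and the 6- and 40-week contacts.
3. Count only a truly unknown live birth as no birth, to match the rule for clinical pregnancy. State that this can bias the comparison if loss differs by arm, and add one sensitivity analysis: multiple imputation, or best and worst case by arm.
4. Analyse the gonadotropin dose actually used in all started cycles, without imputation. Restricting to completed cycles would condition on an event after randomization.
5. Count cycles without retrieval as zero oocytes, and report cancellations by arm.

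The cost is a change of wording and a little more analysis. The data sources are already in the protocol, and the sample size is not affected. The wording should be settled before outcomes are seen.

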## Discussion

IVF is an option for many infertile women, their families and the public, but because of the relatively low success rate, high cost, and possible latent safety problems, new therapies that can improve pregnancy outcomes are highly desirable.

Acupuncture is a frequently used adjunctive therapy for many diseases. The application of acupuncture to IVF has attracted more doctors and patients. Based on the published data, this study will provide significant evidence for using a new method (TEAS) with IVF to improve reproductive outcomes. Although one trial [28] has already reported that TEAS significantly improved the clinical outcome of ET, stimulus frequency, treatment courses or times can be further optimized. Therefore, with appropriate intervention times (from the time of COH to the day of ET), enough treatment courses (six or seven sessions), syndrome differentiation and treatment according to individual characteristics, TEAS may produce a pleasantly surprising result.

In this protocol, we will select the intervention time from COH to ET, from day 3 of the ovarian stimulation cycle to the day of ET to obtain better results. Reasons for this are as follows: 1) the latest meta-analysis demonstrated that acupuncture at approximately the time of COH is the most suitable; 2) according to the studies of Paulus 2002 [4], Westergaard 2006 [7] and Zhang 2011 [28], acupuncture on the day of ET can significantly improve the reproductive outcome of IVF/ICSI; and 3) correcting the state of infertility caused by long-term insufficiency or imbalance requires enough treatment courses.

The control group was based on the fact that any surface stimulation at acupoints, such as acupressure, can cause a physiological reaction or effect [16]. Thus, the control group will not receive any sham TEAS or acupuncture, and they are included mainly as a control group for providing a baseline pregnancy rate. To avoid the psychological placebo effect, every participant will be informed that the TEAS or EA treatments are safe but that procedure effectiveness is unknown.

TEAS or EA frequency is an important issue for consideration. The alternating wave is the most frequently used wave in clinical acupuncture. Therefore, in this trial, we will determine an alternating wave with a relatively broad frequency range (2/100 Hz) for the TEAS or EA intervention. The electrical current is moderate at 0.8 to 1.0 mA for EA and 3 to 5 mA for TEAS based on patient comfort and will not reach the sustain threshold but can obviously be perceived by the patients.

## Trial status

This trial is currently preparing to recruit participants. The enrollment will begin on 1 May 2014 and is expected to be completed before 1 May 2016.

## Abbreviations

CAM: complementary and alternative medical; COH: controlled ovarian hyperstimulation; CPR: clinical pregnancy rate; CRF: case report form; EA: electro-acupuncture; ET: embryo transfer; FSH: follicle stimulating hormone; GnRH: gonadotropin-releasing hormone; hCG: human chorionic gonadotropin; ICSI: intracytoplasmic sperm injection; ITT: intention-to-treat analysis; IVF-ET: in vitro fertilization-embryo transfer; LBR: live birth rate; OA: oocyte aspiration; OCR: oocytes retrieval; PID: pelvic inflammatory disease; RCTs: randomized controlled trials; TCM: traditional Chinese medicine; TEAS: transcutaneous electrical acupoint stimulation; TPP: treated-per-protocol analysis.
